### Recruitment

We elucidate the details of the study to patients during their outpatient visits, concurrently verifying their interest in participation. Simultaneously, we also recruit potential study participants publicly within the institution through informational posters. The clinical researcher or authorized personnel should be able to explain the purpose and treatment of the test and show that they are aware of the benefits and risks of the test in this process. Participants should also be aware that they are required to join voluntarily and maintain the liberty to withdraw from the research at any time. The participants should have enough time to think about their participation before the informed consent form sign and discuss it with their families. The documentation of the discussion and the date of the prior consent shall be recorded in the source documentation. Subjects must write a written consent form. If the hospital that manages the subject’s informed consent does not have the same guidelines, the guidelines that manage the informed consent should be followed equally in all hospitals.

### Sample size

Sample size calculation was based on an assumed proportion of Petersen’s hernia of approximately 1.15% for the conventional close method from our previously published papers [11]. The estimated difference in Petersen’s hernia proportions between close and MEFIX methods was assumed as 0.0% based on the previous similar study [11]. Thus, we set the inferiority threshold at 3% for clinical relevance. Therefore, if the proportion of Petersen’s hernia of the MEFIX method is less than 4.15%, the MEFIX method is not considered inferior to the conventional close method.

A sample size of 199 per arm is required for a proportion test with a one-sided significance level of 0.025 and power of 80% with no difference of hernia proportion between the two methods and a non-inferiority margin for the MEFIX method of 3% (non-inferiority limit = 0.03, treatment A (experimental) group = 0.0115, treatment B (control) group = 0.0115). Further, we decided to increase the sample size by 10% to cover possible dropouts. Consequently, 222 participants were included per group, and a total of 444 were needed. This calculation was performed as the PASS 13 (Power Analysis and Sample Size Software (2014). NCSS, LLC. Kaysville, UT, USA).

### Statistical analysis

All outcomes are assessed using an intention-to-treat analysis that included all patients who were randomly assigned. However, patients who fall under “failure of major entry criteria,” such as those who are not treated at all or do not have available data after randomization, can be excluded from the ITT analysis. Per-protocol analysis also will be performed to evaluate the treatment effect under full compliance.

Demographic data and baseline characteristics of all randomized participants will be pooled. Data will be analyzed using R version 4.2.1 (R: a language and environment for statistical computing, R Foundation for Statistical Computing, Vienna, Austria). Continuous variables will be presented as mean and standard deviation or median and interquartile range. Categorical variables will be described as frequencies and percentages. We will analyze clinicopathological data and postoperative outcomes, including the primary and secondary endpoints, using the chi-square test, Fisher’s exact test, Student’s *t*-test (two samples), or Mann–Whitney *U*-test as appropriate methods based on the type of variables.

To assess the non-inferiority of the MEFIX method compared with the conventional close method, a bilateral 95% confidence interval (CI) of the absolute difference in the Petersen’s hernia rate between the MEFIX group and the CLOSURE group will be estimated. The upper bound of this CI will be compared with the 3% of non-inferiority margin. The primary analysis of the primary endpoint (proportions of bowel obstruction caused by Petersen’s hernia) is performed based on chi-square test without adjustment for imbalance in baseline covariates. And we will calculate the hazard ratio of MEFIX group compared to CLOSURE group by Cox proportional hazard analysis with adjusting covariates. Additionally, secondary endpoints will be analyzed with equivalent test, and dichotomous variables will be compared between the two groups using adjusted and unadjusted hazard ratios and 95% CI by Cox proportional hazard analysis. Unadjusted analyses of time to event for primary and secondary endpoints will be presented using Kaplan-Meier curves and analyzed for non-inferiority of median time to event using the log-rank test. Candidate variables will be subsequently incorporated into a logistic regression analysis. We will express multivariate comparisons as hazard ratios with corresponding 95% CI. For all analyses, *p* < 0.05 will be considered significant statistically. There will be no imputation used to handle missing data during the analysis.

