### Randomization

Patients are randomly assigned in a 1:1 ratio to the MEFIX or CLOSURE group. Allocation is conducted by computer-generated permuted random blocks (size 4) stratified by 12 hospitals. Block randomization is performed by an independent biomedical statistician using R software. A principal investigator (PI) retains the random assignment tables from each hospital. When eligible patients are recruited from each hospital, the clinical research coordinator (CRC) at the PI’s institution is notified. The CRC then confirms the randomization result on the day prior to the surgery and subsequently informs the respective institution.

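### Randomisation is stratified by 12 hospitals, but the tests named for the secondary endpoints ignore hospital, so procedure time and hospital stay lose some precision

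*Protocol article*

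**What the plan says.** Protocol article, Randomization: "Patients are randomly assigned in a 1:1 ratio to the MEFIX or CLOSURE group". The next sentence gives the restriction: "Allocation is conducted by computer-generated permuted random blocks (size 4) stratified by 12 hospitals".

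Protocol article, Statistical analysis: clinicopathological data and postoperative outcomes will be analysed "including the primary and secondary endpoints, using the chi-square test, Fisher’s exact test", the two-sample t-test or the Mann–Whitney test, chosen by type of variable. All four compare two pooled samples. The primary comparison "is performed based on chi-square test without adjustment for imbalance in baseline covariates".

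The same section also plans adjusted analyses. For the primary endpoint, "we will calculate the hazard ratio of MEFIX group compared to CLOSURE group by Cox proportional hazard analysis with adjusting covariates". Dichotomous secondary variables are to be compared by hazard ratios with and without adjustment, and a logistic regression is mentioned. The covariates are not listed. Hospital is not named as a stratum or covariate in any analysis.

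The secondary outcomes include procedure time, bleeding during suturing, hospital stay, and small bowel obstruction and complications within 30 days.

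**The concern.** With blocks of 4 inside each hospital, the arms at a hospital can differ by at most two patients, and then only if its last block is incomplete. Hospital is therefore nearly balanced by design, and differences between hospitals largely cancel out of the treatment contrast. A two-sample test that pools all patients still has those differences in its variance estimate. The standard error it reports is larger than the true sampling error of the difference.

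Procedure time plausibly depends on surgeon and technique, and length of stay on local discharge practice. The Intervention description leaves the direction of anastomosis to the operator's preference, and the eligibility criteria allow laparoscopic or robotic surgery, total or distal resection, and two reconstructions. At stake is the accuracy of the intervals for such outcomes. The article also mentions equivalence testing of secondary endpoints. If that is carried out, needlessly wide intervals directly reduce the chance of showing equivalence.

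**Working it through.** **Inputs from the article.** 12 hospitals, blocks of 4, 1:1 allocation (Randomization). Hernia rate 1.15% in both arms, margin 3%, one-sided 0.025, power 80%, 10% dropout, 222 per arm (Sample size). Procedure time 3.7 ± 1.1 min for MEFIX and 7.5 ± 1.5 min for conventional closure (Background).

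**Assumed.** The ICC is not given. I use 0 to 0.40 for continuous outcomes.

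**The plan's own figure.** n = 2 × 0.0115 × 0.9885 × (1.960 + 0.842)² / 0.03² ≈ 198.3, so 199 per arm. 199/0.9 = 221.1, so 222 per arm and 444 in total. The stated figures reproduce, and nothing below alters them.

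**Continuous outcomes.** Take total variance 1, of which ICC lies between hospitals. Blocking leaves 1−ICC in the true variance of the difference, while the pooled test uses about 1.

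- Width ratio = 1/√(1−ICC)
- Actual size of a nominal 5% test = 2 × [1 − Φ(1.96/√(1−ICC))]

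| Assumed ICC | Width ratio | Actual size |
|---|---|---|
| 0 | 1.000 | 5.0% |
| 0.05 | 1.026 | 4.4% |
| 0.10 | 1.054 | 3.9% |
| 0.20 | 1.118 | 2.8% |
| 0.30 | 1.195 | 1.9% |

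**Check by simulation.** N = 444, 12 hospitals, blocks of 4, 3,000 replicates per setting. Hospitals were either equal in size (37 each) or unequal (5 to 100). Ranges cover both layouts.

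| Assumed ICC | Unadjusted width / hospital-adjusted width | Type I error, unadjusted | Type I error, hospital in model |
|---|---|---|---|
| 0 | 1.00 | 0.044–0.052 | 0.045–0.052 |
| 0.02 | 1.01 | 0.045–0.046 | 0.047–0.049 |
| 0.05 | 1.02 | 0.041–0.045 | 0.047–0.048 |
| 0.10 | 1.05 | 0.042 | 0.051–0.053 |
| 0.20 | 1.10–1.11 | 0.028–0.034 | 0.046–0.054 |
| 0.40 | 1.25–1.27 | 0.015–0.016 | 0.043–0.047 |

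At a true 5% level the Monte Carlo standard error is √(0.05 × 0.95/3000) ≈ 0.004. The simulated widening is slightly below the formula at the higher ICCs (at 0.40 the formula gives 1.29), so the formula is a mild upper estimate with only 12 hospitals.

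**Procedure time, in minutes.** Treat the article's SDs as total SDs and take 199 per arm. SE = √[(1.1² + 1.5²)/199] = √(3.46/199) = 0.132, so the 95% half-width is 1.96 × 0.132 = 0.26. With hospital in the model it is 0.26 × √0.8 = 0.23 at ICC 0.20, or 0.26 × √0.6 = 0.20 at ICC 0.40. The expected difference is 7.5 − 3.7 = 3.8 min, about 29 unadjusted standard errors.

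**Primary endpoint.** Expected events are 444 × 0.0115 = 5.1. If the hospital hernia rates have a coefficient of variation CV, then ICC ≈ CV² × 0.0115/0.9885. Even CV = 1.5 gives 0.026 and a width ratio of 1.013. Simulating the 1.15% rate with CV from 0 to 1.5, the unstratified standard error divided by the true SD of the estimate was 0.99 to 1.01. There is no measurable widening.

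**The case against.** The strongest reply is that little depends on this. The error is conservative, the procedure-time comparison would come out the same way with or without hospital, and the size rests on an ICC that the article does not report. Near zero the effect vanishes: 1% at ICC 0.02. All of that stands, and it limits the point to precision.

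The article also already plans adjusted hazard ratios for dichotomous outcomes. That covers bleeding and 30-day complications, and hospital may be among the covariates. A covariate list is commonly left to the SAP, so its absence is not a fault. For these outcomes the point therefore reduces to making sure hospital is used somewhere. Procedure time and hospital stay have no stated adjusted analysis, so the mismatch is clearest there.

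Three stronger readings are tempting but unsupported:

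- **That the primary non-inferiority test is compromised.** The calculation shows no measurable effect. With about five events, a stratified primary analysis could be unstable, so leaving it unadjusted is a reasonable choice.
- **That the loss falls mainly on outcomes where MEFIX is expected to do better, including stay.** The Discussion and Conclusions claim shorter operating time, less kinking and fewer complications such as bleeding. They do not predict a shorter stay. The Background remark on stay compares laparoscopic with open surgery.
- **That the binary secondary outcomes will get no adjusted analysis.** The Statistical analysis section says otherwise.

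**Conclusion.** The point holds for the secondary endpoints only. The named tests do not reflect the stratified allocation, so outcomes that vary between hospitals get intervals that are too wide and tests that are too cautious. At an ICC of 0.20 the unadjusted interval from 444 patients is about as wide as an adjusted interval from 444 × 0.8 ≈ 355.

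This rests on an assumed ICC and on between-hospital variation being plausible for procedure time and stay. The article establishes neither. For bleeding and complications there is even less basis for choosing a value. The non-inferiority conclusion, the sample size and the expected conclusion on procedure time are unaffected. It is a modest, inexpensive improvement and not a threat to validity.

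**What to change.** - **Procedure time and hospital stay:** use a linear model with arm and hospital, with stay on the log scale. If a rank test is preferred for stay, its hospital-stratified form (van Elteren) serves the same purpose.
- **Bleeding and 30-day complications:** report a Mantel–Haenszel risk difference stratified by hospital, pooling small hospitals where strata are sparse. Alternatively, state that hospital is a covariate in the adjusted models already planned.
- **Primary endpoint:** keep the unstratified interval. A stratified risk difference may be added as a sensitivity analysis only.

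The cost is a change of wording and slightly more analysis work. Hospital is known for every patient from randomisation, so no new data or patients are needed. The linear models use 11 degrees of freedom for 12 hospitals, which is trivial at this sample size. The real downside is sparse strata for rare events, hence the pooling rule. The article reports recruitment at 37% and places the final analysis after the last participant's three-year follow-up, so there is time to pre-specify this.

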### Study design and participants

This study was designed as prospective, single-blind, non-inferiority randomized controlled multicenter trial in Korea. We enroll patients with histologically diagnosed gastric cancer of clinical stages I, II, or III who underwent B-II or REY anastomosis after laparoscopic or robotic gastrectomy. Patients who meet the inclusion criteria are randomly assigned to two groups: a CLOSURE group that underwent conventional Petersen’s defect closure and a MEFIX group that underwent the mesenteric fixation method. Computed tomography (CT) will be performed every 6 months for the first 3 years after surgery and every 1 year for the next 2 years. A history of outpatient or emergency department visits for symptoms of internal hernia, such as vomiting and abdominal pain, or emergency surgery for internal hernia will be examined (Fig. 2 and Table 1).

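### Two non-equivalent procedures are given for the primary endpoint; the equality chi-square test carries the primary label, and no sentence says that the confidence-interval rule decides

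*Protocol article*

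**What the plan says.** The design is stated as non-inferiority in Study design and participants: "This study was designed as prospective, single-blind, non-inferiority randomized controlled multicenter trial in Korea". The Sample size section uses a "proportion test with a one-sided significance level of 0.025 and power of 80" per cent, "with no difference of hernia proportion between the two methods and a non-inferiority margin for the MEFIX method of 3" per cent. Both arms are planned at 1.15%: "treatment A (experimental) group = 0.0115, treatment B (control) group = 0.0115".

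Three statements in the Statistical analysis section bear on how the primary endpoint is tested:

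- A general list of tests: "We will analyze clinicopathological data and postoperative outcomes, including the primary and secondary endpoints, using the chi-square test", Fisher's exact test, the t-test or the Mann-Whitney test, according to the type of variable.
- The non-inferiority rule, a two-sided 95% confidence interval for the absolute difference in hernia rate: "The upper bound of this CI will be compared with the 3% of non-inferiority margin".
- Directly after that, the primary analysis of the primary endpoint is said to be one that "is performed based on chi-square test without adjustment for imbalance in baseline covariates".

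The same section sets p < 0.05 as the significance threshold for all analyses. It describes no margin-shifted version of the chi-square test and does not rank the interval rule and the chi-square test.

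**The concern.** The two procedures test different hypotheses. The interval rule tests the null that MEFIX is worse by at least 3 points. The chi-square test, as ordinarily understood, tests the null that the rates are equal, which in this trial is the planning alternative. A significant chi-square result would show that the arms differ. A non-significant one shows only that a difference was not detected, and with about two events expected per arm that outcome is close to assured when the methods perform alike.

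The label matters because the analysis called primary is the one a reader expects to settle the trial. With both procedures on the page and no ranking, the article leaves room to choose after the data are seen, and the two can point in opposite directions close to the margin.

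**Working it through.** **Inputs.** From Sample size: rate 1.15% in each arm, margin 3 points, one-sided alpha 0.025, power 80%, 199 per arm, 10% dropout, 222 per arm. From Randomization: 1:1 allocation. Assumption: the chi-square test is the Pearson test of equal proportions without continuity correction, since no other form is described.

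**Step 1: reproduce the plan's sample size.** With unpooled variance,

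n = (1.960 + 0.842)² × [2 × 0.0115 × 0.9885] / 0.03² = 198.3, rounded up to 199.

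With dropout, 199 / 0.90 = 221.1, rounded up to 222. Both stated figures are reproduced. The sample size therefore belongs to the interval-against-margin rule. Exact binomial enumeration agrees: with a Wald interval and both rates at 1.15%, the upper limit falls below 3% in 80.7% of trials at 199 per arm, in line with the stated 80%.

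**Step 2: what the chi-square test would have needed.** To detect 4.15% against 1.15% at two-sided 0.05 with 80% power, an equality test needs 449 per arm. Its approximate power is 46% at 199 and 50% at 222. The trial was not sized for it.

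**Step 3: chi-square behaviour by exact enumeration.** Binomial probabilities were summed over the possible pairs of event counts.

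| True rates, MEFIX and CLOSURE | Event | 199 per arm | 222 per arm |
|---|---|---|---|
| 1.15%, 1.15% | p < 0.05 | 4.4% | 4.6% |
| 4.15%, 1.15% (at the margin) | p > 0.05 | 53.6% | 48.3% |

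Half of the 4.4% are results that favour CLOSURE. With a Yates correction or Fisher's test, the figures at 199 per arm are 0.7% and 66%.

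**Step 4: two data sets at 199 per arm.** With equal arms of size n, d the difference in event counts and m the total events, Pearson chi-square = 2n·d² / [m(2n − m)].

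- 2 against 2 hernias: chi-square = 0, p = 1.00. Wald upper limit = 0 + 1.96 × √(2 × 0.01005 × 0.98995 / 199) = 1.96%. Non-inferior by the interval rule; the p-value says nothing about that.
- 8 (MEFIX) against 2: chi-square = 398 × 36 / (10 × 388) = 3.69, p = 0.055. Difference = 6/199 = 3.0 points. Wald upper limit = 3.02 + 1.96 × 1.56 = 6.1 points. Non-significant by chi-square, yet non-inferiority clearly fails by the interval rule.

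**Step 5: sensitivity to the interval method, which the article does not name.**

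| Method | Power at 1.15% in both arms, n = 199 / 222 | Non-inferiority declared at 4.15% and 1.15%, n = 199 |
|---|---|---|
| Wald interval | 81% / 82% | 4.4% |
| Score test (Farrington-Manning) | 56% / 65% | 1.7% |

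**The case against.** The strongest reply is that the article already contains the right test. The interval rule is introduced for the stated purpose of assessing non-inferiority, is specific about margin and limit, and agrees with the one-sided 0.025 sample size. The chi-square sentence is qualified by the absence of covariate adjustment and is followed by a covariate-adjusted Cox model. It may therefore be meant only to separate the unadjusted comparison from the adjusted one. The general test list is generic and weak evidence about the primary decision.

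Most of this stands. A reader might infer that the trial has no valid non-inferiority analysis, or that it will declare MEFIX non-inferior whenever p > 0.05 and so be wrong about half the time at the margin. The document supports neither. The valid rule is on the page, and nowhere is p > 0.05 equated with non-inferiority or p < 0.05 required for it.

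The reply does not remove the conflict of labels. The chi-square test is explicitly tied to the primary analysis of the primary endpoint, and a p < 0.05 threshold is applied to all analyses. The section on data monitoring and interim analysis also frames the primary outcome through p-values, both for the interim looks and for the final analysis. If the milder reading is the intended one, saying so costs nothing.

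**Conclusion.** The point holds in a limited form: one section gives two procedures that are not equivalent, attaches the primary label to the one that cannot test the trial's hypothesis, and does not state which decides. The defect is one of labelling and precedence, not the absence of a valid analysis.

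The size is conditional on the chi-square p-value being used for the verdict. In that case, at 199 per arm, p < 0.05 would occur in about 4% of trials with both rates at 1.15%, against the 80% power planned. At the margin, p > 0.05 would occur in about 54% (48% at 222 per arm), against a nominal 2.5% chance of wrongly declaring non-inferiority. If the interval rule decides, none of these error rates applies.

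The result rests on reading the chi-square test as the ordinary equality test and on the article's own planning rates. A separate analysis plan could settle the precedence; the point concerns what the article itself states.

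**What to change.** In Statistical analysis, name the comparison of the upper limit of the two-sided 95% confidence interval for the risk difference with 3% as the sole primary analysis, with non-inferiority concluded only if that limit lies below 3%. State that any unadjusted chi-square or Fisher p-value for the primary endpoint tests equality, is supportive only, and plays no part in the non-inferiority verdict. Bring the general list of tests earlier in the section into line.

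The cost is a few sentences of wording. The planned 199 per arm, or 222 with dropout, is unchanged, because it was derived for this rule.

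The choice of interval method should be kept separate from this relabelling. A score method holds the error at the margin better than Wald (1.7% against 4.4% at 199 per arm), but its exact power is only about 56% at 199 and 65% at 222. Adopting it would mean restating the 80% power, so it should not be brought in as part of the wording change.

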## Conclusions

This study is a prospective, randomized controlled trial to compare the MEFIX and CLOSURE methods, intending to confirm that the MEFIX method is not inferior to the CLOSURE method. If the results are positive, the MEFIX method could prevent Petersen’s hernia and reduce operation time and complications. Moreover, the MEFIX method is a new concept and technique that have not been previously reported. It is anticipated to be applicable not only in gastric cancer surgery but also in bariatric surgery, especially in Roux-en-Y gastric bypass procedures.

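### Several supportive and secondary analyses are wrong as written (non-inferiority of a median that is never reached, hazard ratios from logistic models, Cox models where no event time exists); the primary non-inferiority decision is unaffected

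*Protocol article*

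**What the plan says.** All the statements at issue stand in the Statistical analysis section of the protocol article.

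- **Primary decision.** The upper bound of a two-sided 95% confidence interval for the absolute difference in hernia rate is compared with 3%. The primary analysis is unadjusted. A Cox model with covariates is added.
- **Time to event.** Kaplan-Meier curves for primary and secondary endpoints are to be "analyzed for non-inferiority of median time to event using the log-rank test". No margin on a time or hazard-ratio scale is given.
- **Multivariable models.** Candidate variables are "incorporated into a logistic regression analysis. We will express multivariate comparisons as hazard ratios".
- **Secondary endpoints.** The plan states that "secondary endpoints will be analyzed with equivalent test, and dichotomous variables will be compared between the two groups using adjusted and unadjusted hazard ratios". The paragraph before it lists chi-square, Fisher, t and Mann-Whitney tests for primary and secondary endpoints alike.

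The Sample size section takes an "assumed proportion of Petersen’s hernia of approximately 1.15% for the conventional close method" and no difference between arms. The Secondary outcomes list includes procedure time and bleeding during the mesenteric suture. The Conclusions section says that, if results are positive, "the MEFIX method could prevent Petersen’s hernia and reduce operation time and complications".

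**The concern.** These are not details left to a later analysis plan. The article fixes each of them, and five do not fit the data the trial will produce or the claim it wants to make:

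1. A median cannot be compared when almost nobody has the event, and a log-rank test of equality does not test non-inferiority.
2. A logistic model yields odds ratios, not hazard ratios.
3. A covariate-adjusted Cox model is planned on a handful of events.
4. Hazard ratios are assigned to binary outcomes, some of which occur during the operation and have no follow-up time.
5. The test for secondary endpoints is described in two ways. One of them, if it means equivalence, has no margin and cannot show that MEFIX is faster.

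The practical risk lies in the first. The plan applies p < 0.05 to all analyses, so a non-significant log-rank result could be presented as support for non-inferiority when it only reflects too few events.

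**Working it through.** **Inputs.** Sample size section: "non-inferiority limit = 0.03, treatment A (experimental) group = 0.0115, treatment B (control) group = 0.0115"; one-sided alpha 0.025; power 80%; 199 per arm, 222 after 10% dropout. Background: cited hernia incidence up to 9.7%; earlier closure times 3.7 (SD 1.1) and 7.5 (SD 1.5) min. Data collection: primary endpoint at 3 years, follow-up to 5 years.

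**The plan's own figure.** n = 2p(1−p)(1.960 + 0.842)²/0.03² with p = 0.0115 gives 198.3, rounded up to 199. Then 199/0.9 = 221.1, rounded up to 222. Both reproduce, and nothing below changes them.

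**1. Median and log-rank.** A median requires half of an arm, about 111 of 222. Implied exponential median = 3 ln 2 / [−ln(1−p)] years (constant hazard assumed).

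| 3-year rate | Expected events per arm of 222 | Implied median |
|---|---|---|
| 1.15% (planned) | 2.6 | about 180 years |
| 4.15% (non-inferiority limit) | 9.2 | about 49 years |
| 9.7% (highest cited) | 21.5 | about 20 years |

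The probability that half an arm has the event is below 10⁻⁵⁰ in each row.

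Adding a hazard-ratio margin would not rescue the test. The 4.15% limit against 1.15% corresponds to ln(0.9585)/ln(0.9885) = 3.66. Showing non-inferiority on that scale with 80% power needs about 19 events (Schoenfeld formula). With 4.6 to 5.1 expected, power is about 28 to 31%.

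To size the risk of misreading, I simulated a true MEFIX rate exactly at the limit (4.15% against 1.15%, 222 per arm, exponential times, 3 years, no dropout). The log-rank test was non-significant at two-sided 0.05 in about 48% of trials.

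**2. Logistic model and hazard ratio.** At 4.15% against 1.15% the odds ratio is (0.0415/0.9585)/(0.0115/0.9885) = 3.72 and the hazard ratio 3.66, so for the rare primary endpoint the mislabelling does little numerical harm. For commoner outcomes they separate: at 20% against 10% (assumed for illustration) they are 2.25 and 2.12.

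**3. Adjusted Cox model.** Expected events in total: 0.0115 × 398 = 4.6, or 0.0115 × 444 = 5.1. Chance that one arm has none: 0.9885¹⁹⁹ = 0.100, or 0.9885²²² = 0.077. Chance that at least one arm has none: 1 − (1 − 0.100)² = 19%, or 1 − (1 − 0.077)² = 15%. The ordinary estimate is then zero, infinite or undefined. With about five events, the standard error of the log hazard ratio is about 2/√5.1 = 0.89, so the 95% interval extends a factor of about 5.7 either way before any covariate enters.

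**4. Endpoints without an event time.** Bleeding during the suture is a yes/no observation made in the operating room. There is no time origin, censoring or follow-up for a Cox model to use.

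**5. Test for procedure time.** From the earlier data the difference is 7.5 − 3.7 = 3.8 min, with SE = √[(1.1² + 1.5²)/222] = 0.125 min and z about 30. A t-test for a difference therefore has power near 100%. Two one-sided equivalence tests at 0.025, with an assumed margin because none is stated, pass about 0% of the time at margins of 1 to 3 min, 2.5% at 3.8 min and about 100% at 5 min. Passing at any margin would not show that MEFIX is quicker.

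**The case against.** The best defence is that none of this touches the trial's conclusion. The primary decision rests on the risk-difference interval against 3%, the sample size matches that analysis, and a misread log-rank test would not alter the prespecified rule. This stands, and it limits the severity.

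Four stronger readings are tempting, and the document does not support them.

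- **That the supportive analyses cannot be computed at all.** Only the median comparison is impossible. Kaplan-Meier curves can be drawn and a log-rank p-value obtained. Both arms have at least one event in about 81 to 85% of trials at the planned rate, and an imprecise treatment-only Cox hazard ratio is then estimable.
- **That the regression plan as a whole is unsound.** A Cox model is also planned and does give hazard ratios, so the logistic sentence is probably a labelling slip. It still leaves unclear which model produces the adjusted result.
- **That the secondary claims rest on the wrong hypothesis.** The wording of the secondary test is ambiguous and may only mean the corresponding test. The preceding paragraph already names difference tests that can show MEFIX is faster. On complications, the Abstract speaks of no increase, not only of a reduction. What remains is two descriptions to reconcile and no stated margin.
- **That ignoring the hospital strata is an error.** Allocation is "stratified by 12 hospitals", and an unadjusted analysis after stratified allocation is normally conservative, not invalid. Modelling hospital may gain precision, but the document gives no figure from which to size the gain.

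**Conclusion.** The point holds for supportive and secondary analyses only, at moderate severity. The comparison of medians cannot be carried out for the primary endpoint at any event rate the article names, and the log-rank test does not assess non-inferiority. Reporting logistic results as hazard ratios, and giving hazard ratios for outcomes with no event time, are errors as written. The covariate-adjusted Cox model for the primary endpoint is not supportable on about five events. The secondary-endpoint test is described inconsistently.

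The event counts rest on the plan's 1.15% in both arms ("The estimated difference in Petersen’s hernia proportions between close and MEFIX methods was assumed as 0.0"%) and on 398 to 444 patients with outcome data. The implied medians and the 48% figure also assume a constant hazard. The conclusion about the median survives even at 9.7%. The Cox conclusion would soften if events were far more frequent than planned.

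**What to change.** Amend the wording of the Statistical analysis section as follows.

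1. Delete the non-inferiority comparison of medians by log-rank. Keep the Kaplan-Meier curves and report the 3-year cumulative incidence difference with its 95% confidence interval as a supportive estimate beside the primary analysis.
2. Label logistic results as odds ratios and keep hazard ratios for Cox models.
3. For the primary endpoint, limit the Cox model to treatment alone, for example with Firth penalisation so that an arm without events still gives a finite estimate, or drop it.
4. For binary endpoints without an event time, such as bleeding during the suture, report risk differences with 95% confidence intervals.
5. Name one test per secondary endpoint, and state that procedure time is compared for a difference (superiority). If equivalence is really meant for some endpoint, say which and give its margin.

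Using hospital as a factor or stratum in the secondary analyses is optional.

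The cost is a wording amendment before the final analysis. Sample size, data collection and the primary decision rule stay as they are.
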